**Figure 2 F2:**
[figure not shown]
**Evaluation design accounting for seasonal differences and using a waiting list control**. CONT = gym lessons (existing state-sponsored programme). INT = participatory parent-focused intervention plus simultaneous gym lessons. X1 and X2: randomization time points, X1 = autumn, X2 = spring. ---- children enrolled and measured, but no intervention/gym lessons.

Preschool assignment was blinded through the use of sequentially numbered, sealed envelopes. Preschools in the control arm (CONT) (n = 20; 371 children) receive the state-sponsored programme's gym lessons over six months as the sole intervention. Parents of children enrolled at preschools in the intervention arm (INT) (n = 17; 370 children) receive the participatory intervention, while their children also participate in the gym lessons. The participatory parent-focused intervention runs simultaneously with the gym lessons over the first six months, but continues for a total of at least nine months.

To account for seasonal differences in physical activity [34,35], the study was implemented at two time-points during the year: half of the preschools started the intervention in autumn 2008 with the other half starting in the spring 2009. To account for changes that occur as a consequence of physical maturation in children over time, the participatory intervention arm served as waiting list control during the first six months. Due to the participatory nature of the intervention, it was not possible to blind study participants or intervention providers. However, those involved in outcome assessment will be blinded to intervention assignment.

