### Evaluation Design

Our study uses a cluster-randomized trial design, with natural preschool-bound clusters of children randomized to either the intervention or control arm. The evaluation strategy combines both quantitative and qualitative data collection and analyses. Quantitative outcome measurements will be obtained before the start of the intervention (baseline assessment), 6 months after baseline assessment (at the end of the state-sponsored gym lesson programme) and at 12 months after baseline assessment. Qualitative data collection, described in greater detail below, will allow for a closer examination of variation in the implementation process across and within intervention sites. In reporting our study, we will account for the recommendations of the CONSORT statement concerning complex cluster-randomized trials [31,32]. Baseline data from the completed recruitment to the study will be reported elsewhere.

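### The text below Figure 2 calls the whole intervention arm a waiting-list control for the first six months, contradicting its own account of that arm's treatment in the same period

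*Protocol article*

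**What the plan says.** The statements on who receives what, and when, are these:

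- **Treatment of the intervention arm** (Recruitment and randomization, below Figure 2): "The participatory parent-focused intervention runs simultaneously with the gym lessons over the first six months, but continues for a total of at least nine months". The Figure 2 legend agrees: "INT = participatory parent-focused intervention plus simultaneous gym lessons".
- **Waiting list** (next paragraph): "the participatory intervention arm served as waiting list control during the first six months". The reason given is to allow for the children's maturation. No wave or subset is named. The legend has a dashed line for "children enrolled and measured, but no intervention/gym lessons", and its text does not say to which preschools the line belongs.
- **Staggered start** (same paragraph): "half of the preschools started the intervention in autumn 2008 with the other half starting in the spring 2009". The legend gives two randomisation time points, X1 in autumn and X2 in spring.
- **Visits** (Evaluation Design): baseline comes before the intervention starts, the second measurement 6 months later when the gym lessons end, and the third at 12 months.
- **Contrast** (Abstract, Research Questions): gym lessons supplemented by the parent programme are compared with gym lessons alone. The primary question concerns accelerometry at 6 months.
- **Primary model** (Assessment of intervention effectiveness): the listed covariates are age, sex, SES, immigration status and baseline BMI or counts. Autumn versus spring start appears only as a subgroup factor.

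**The concern.** Two adjacent paragraphs describe the same arm over what reads as the same six months, once as treated with both programmes and once as waiting. The legend's dashed line suggests that waiting means receiving neither programme. A reader who takes the waiting-list sentence at its word would conclude that the first 6-month comparison sets no programme against gym lessons, which is not the question the trial asks.

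The waiting list is not a passing remark. It is in the title of Figure 2, and the Discussion offers a cluster-randomised design with a waiting list as a possible model for other evaluations. Anyone analysing or copying the design needs to know who waited, and whether measurements from the waiting period can enter the 6-month comparison.

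**Working it through.** **The plan's figure.** No number is in dispute. The sample size reproduces from the inputs under Sample size and power considerations (difference 19.05, SD 38.1, ICC 0.1, power 0.9, two-sided alpha 0.05):

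- Per arm, unclustered: 2 × (1.960 + 1.2816)² / 0.5² = 84.06.
- Children per school: 504 / 24 = 21. Design effect: 1 + (21 − 1) × 0.1 = 3.0.
- Total: 2 × 84.06 × 3.0 = 504.4, against 504 stated. With 10% loss: 504 / 0.9 = 560, as stated.

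This calculation assumes a difference between arms without saying what the intervention arm has received by month 6, so it cannot settle the point.

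**Timelines for the intervention arm, in months from baseline.** The gym lessons last six months, the parent programme at least nine, and the last measurement is at month 12.

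| Reading | Gym lessons | Parent programme | Contrast at month 6 |
|---|---|---|---|
| Concurrent | 0 to 6 | 0 to 9 or later | both programmes vs gym lessons |
| Whole arm waits | 6 to 12 | 6 to 6 + 9 = 15 or later | neither programme vs gym lessons |

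On the second reading the programme would still be running at the last measurement. Research question 1 (effect at 6 months) and question 5 (effect maintained from 6 to 12 months) could not be answered. The two rows are incompatible.

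**Does the staggered start rule out a wait by the whole arm?** The word half does not do so alone: 20 control and 17 intervention preschools are 20/37 = 54% and 17/37 = 46%, so controls in autumn and intervention preschools in spring would also be roughly half and half. Two other statements tell against that split. Randomisation is shown at both time points, which would serve no purpose if season fixed the arm. The planned autumn-versus-spring subgroup analysis needs both arms in each season. With both arms in each wave, some intervention preschools started in autumn 2008 and did not wait.

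**Where baseline falls.** The 6-month visit is at the end of the gym lessons, and the lessons last six months. Baseline is therefore as the lessons start, after any wait. A preschool measured untreated beforehand would have a further measurement besides the three listed under Evaluation Design, and the text gives that measurement no role.

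**When the wait falls.** If the spring preschools were randomised at X2, any wait before X2 came before they had an arm, so it could not belong to the intervention arm. The text does not say which applies.

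**The case against.** The strongest defence is that one badly worded sentence stands against everything else. The Abstract, Evaluation Design, Research Questions, allocation text and legend all give the same contrast, and baseline can be worked out from the visit schedule. The waiting-list sentence directly follows the one on autumn and spring starts, so the first six months may mean calendar time from autumn 2008, with only the spring starters untreated then. Figure 2 is not reproduced in the text reviewed and may show exactly this. The article is also condensed, so the handling of wave and of waiting-period data may be set out in a fuller plan.

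Most of this stands. The intended contrast can be inferred, and neither the missing figure nor the absence of a wave term is held against the plan. The printed sentence is not rescued, however: it names the intervention arm, and on the charitable reading it should name a wave.

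A reader might go further and infer that arm is confounded with season, that the arm effect is not identified, or that season could account for much of the 19.05-count target. The documents do not support this. Two randomisation time points and the timing subgroup argue against confounding, and no seasonal difference in counts is given from which to size a bias. Nor does the analysis section say that waiting-period data serve as control data.

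**Conclusion.** The contradiction is real and confined to the description of the design. The waiting-list sentence cannot hold for the whole intervention arm alongside the concurrent programme, the two randomisation time points and the stated 6-month contrast. The primary comparison itself can be recovered with reasonable confidence.

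The size is qualitative: no sample size, effect size or error rate changes, and no bias can be quantified from the documents. What remains open is which preschools waited, from when, on which side of randomisation, and what their extra measurements are used for. The view that only the spring-2009 starters waited is an inference from the order of the sentences and the legend, not a statement in the text.

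**What to change.** 1. Reconcile the two paragraphs below Figure 2 by stating which preschools had an untreated measured period, from which date, and whether it came before or after their randomisation.
2. State that baseline is, for every preschool, the last measurement before either programme starts. This makes explicit what the visit schedule already implies.
3. Include randomisation wave (autumn or spring) as a term in the primary multilevel model, so that the arms are compared within the wave in which they were randomised.
4. State that waiting-period data serve only to describe maturation and season and do not enter the primary contrast.

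The cost is one corrected paragraph, one model term and one analysis rule. No new data are needed. Items 3 and 4 can go in the analysis plan if they are not already there.

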### Measurements

The unit of analysis are children between three and six years of age enrolled at the participating preschools. Because the evaluation of intervention effectiveness requires application of a lightweight monitor to record PA and heart rate (Actiheart, CamNtech, Cambridge, UK) to the anterior chest wall as described below, children with severe atopic dermatitis, serious physical malformations or disabilities are neither assessed nor contribute data to the evaluation.

#### Physical intensity

We assess physical activity using one-dimensional accelerometry in the vertical plane, measured over six consecutive days including two weekend days (Actiheart, CamNtech, Cambridge, UK). The Actiheart device has been specifically selected for use in this study because its technical validity and reliability has been established [36] and because it allows recording epochs to be set to intervals of 15, 30 or 60 seconds [37]. In our study, we use an epoch setting of 15 seconds to enable detection of rapid changes in movement intensity and short bursts of moderate-to-vigourous physical activity typically exhibited by young children [38,39]. For transformation into an outcome providing a summary measure of the *intensity *of physical activity, accelerometry counts for every 15-second interval during the six-day measurement will be averaged to a single grand mean value for each child.

According to the measurement protocol, the Actiheart monitors are programmed and securely affixed to each child's substernal thorax [40] by two sticky electrodes (Kendall Arbo*ECG electrodes, Tyco Healthcare, Neustadt Donau, Germany) and additional tape. Subsequently, children participate in a standardized circle-running test for the assessment of heart rate recovery (see below). The monitors stay in place for the next six days; at the end of the recording period, monitors are returned to the research team together with the parental questionnaires in sealed envelopes. In contrast to our expected participation rate of about 60%, almost all children present in the preschool at the measurement day insisted on participating and wearing the device (see figure 3).

**Figure 3 F3:**
[figure not shown]
**Preschool children happily presenting their accelerometer**.

#### Anthropometry and body composition

Height is measured to the nearest 0.1 cm (Seca Deutschland, Hamburg, Germany), and weight measured to the nearest 0.1 kg (Soehnle pharo, Nassau, Germany) in underwear following a standardized protocol. Body mass index is calculated using weight (kg) divided by the height squared (m^2^). Instead of using age-specific BMI z-scores, we control for the age-related changes in BMI by inclusion of age as a covariate in the multilevel analyses.

Waist circumference is measured directly on the skin half-way between the top of the iliac crest and the lower rib at the end of gentle expiration [41] with an accuracy of 0.5 cm using a flexible, non-elastic measuring tape (Seca Messband 201, Seca Deutschland, Hamburg, Germany). In addition, waist-to-height-ratio is calculated and serves as a secondary outcome in the analysis of intervention effectiveness [42-44]. Triceps, biceps, subscapular, vertical hip and calf skin folds are measured at least twice using Lange Skin Fold Calipers (Beta Technology, Santa Cruz, USA) with measures averaged for each site. These mean measures will be summed to create an additional secondary outcome - the skin fold sum [45,46]. The quality of the anthropometric measures is ascertained by 1) standardized training sessions for all study personnel conducted over three days and repeated regularly; 2) duplicate measurement of two children per preschool for continuous assessment of interrater reliability and 3) use of a limited number of experienced study personnel to perform skin fold measurements.

#### Parent Questionnaire

A review of previous work assessing health-related behaviours of preschool children by parental proxies revealed few instruments with established psychometric properties. Whenever possible, we use items from existing surveys; in other cases, it was necessary to adapt items to clarify selected features and those specifically related to the intervention. The resulting survey, described below, focuses primarily on children's health behaviours and is completed by one or both of the child's parents. The survey was administered at baseline, six and 12 months and will enable a complementary assessment of intervention effectiveness.

##### Physical activity of the family

Children's PA and sedentary behaviour (e.g., time spent watching television) is being measured using questions from a simple survey instrument that has been validated against a motor skills test [47]. The family's active leisure time is also explored using questions like "How often do you go on excursions (zoo, forest, park, etc.) with your child?" and "How often do you go outside with your child?" Other questions assess parents' leisure time physical activities to establish normative behaviour at baseline. Subsequent assessments will enable an evaluation of potential effects of the participatory intervention on the parents themselves.

##### Nutrition

Childrens' nutrition has the potential to affect most of the secondary outcomes of this study (BMI, skin folds). Therefore, nutrional status is being analyzed as a confounder. Rather than measuring actual caloric intake of the children, however, we focus on the consumption of foods that generally reflect on lifestyle choices. Specifically, we assess the consumption of fruits and vegetables as measured by questions adapted from Bayer et al. [48]: "How many portions (size of a child's hand) of fruit/vegetables does your child eat on average per day?". The consumption of sugared drinks and sweetened or high-caloric snacks is assessed by an adaptation of a food-frequency questionnaire. The food-frequency questionnaire also contains items on a range of indicator foods (fast food, deep-fried) foods, high-caloric food, food especially advertised as healthy for children) and their degree of consumption.

##### Intervention-specific items

Intervention-specific questions evaluate the feasibility of the intervention. For example, to be feasible, the "walking bus" project idea requires a walkable distance between the child's home and the preschool as well as relatively safe traffic conditions. Feasibility is assessed by project-specific items such as "How long does it take you to walk with your child to the preschool?" ("< 5 minutes", "5-10 minutes", "10-15 minutes", "15-20 minutes", "> 20 minutes") and "Are traffic conditions in your neighbourhood safe enough to allow your child to play in the street with other children?" (yes/no).

#### Heart rate recovery

Two-channel electrocardiography using the short-term mode of the Actiheart device (Actiheart, CamNtech, Cambridge, UK) assessed heart rate recovery (HRR), a parameter of cardiovascular fitness and a predictor of mortality in adults [49]. HRR has been traditionally defined by the reduction in heart rate 1 and 3 minutes after a period of submaximal exercise on the treadmill, relative to the peak heart rate at the end of the exercise. In adolescents, HRR is associated with cardiovascular risk factors like serum glucose, triglyceride and CRP levels [50]. Owing to the absence of a valid fitness test in preschool children, an association of HRR with cardiovascular risk or fitness in preschool children has not been previously established[51]. HRR was therefore included for descriptive and exploratory analyses only.

We adapted the traditional measurement protocol for HRR to the field setting in preschools by assessing heart rate after 3 minutes of rest, 2 minutes of circle-running with maximal exertion and again after 3 minutes of rest. The peak heart rate was defined as the highest heart rate in the final 60 seconds of running. HRR is being measured at one and three minutes after the end of exercise. The circle-running test is conducted with at least five and no more than ten children at a time. In a preceding pilot study with 33 preschool children, the latter range was found to be optimal in reducing interferences among children while the test is being conducted.

### Outcomes

#### Quantitative assessment

##### Primary Outcome

• Mean accelerometry counts per 15 seconds over six days of measurement

##### Secondary outcomes

• BMI

• Skin fold sum and central body fat (waist-to-height ratio)

• Physical activity (PA) behaviour via parent questionnaire [47]

##### Other measurements

• Nutritional behaviour, media use

• Heart rate recovery (HRR) after postmaximal exercise

### Research Questions

We aim to show that the supplementation of state-sponsored gym lessons with a parent-focused participatory intervention:

1) leads to significantly increased physical activity intensity in preschool-aged children at 6 months compared with baseline, as measured by accelerometry

2) leads to significant decreases at 6 months compared with baseline in childrens' mean BMI, sum of skin folds and waist-to-height ratio

3) leads to significant improvement in childrens' PA behaviour at 6 months as assessed by questionnaire

4) leads to a significant increase from baseline in childrens' mean 1-minute heart rate recovery after submaximal exercise at 6 months

5) has sustained effects on primary and secondary outcomes stated above (i.e., no significant difference between 6 and 12 months measurements)

Research questions to be addressed using *qualitative techniques *include:

1) How well is the participatory intervention accepted and adopted by parents and teachers?

2) To what extent do participants feel the parent-focused participatory intervention is tailored to the local needs?

3) Do participants feel that the participatory intervention is feasible in the German preschool setting within the framework of an existing state-sponsored programme?

4) What are the barriers and facilitating factors that appear to impede or promote successful intervention implementation and outcomes?

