#### Indicators of intervention adoption and implementation

According to the RE-AIM framework [61,62], evaluations of health promotion interventions should not only focus on efficacy, but should include other dimensions of quality like intervention adoption, implementation and maintenance. In our study, the intervention adoption is being assessed by structured interviews with the head teachers before the intervention start and was rated over all preschools on a 1-100% scale. The extent to which the intervention was implemented at each site is assessed by the external PA teacher delivering the state-sponsored gym programme. This external teacher documents numerous features of the implementation process, including the number of project ideas chosen and finally realized, the number of meetings with parents, the participation rate at these meetings, the barriers and resources perceived by parents and teachers, the social environment and development of issues related to effective communication (e.g. atmosphere during meetings, involvement of immigrant parents, coordination between parents and teachers). In addition, information on implementation gathered during the head teacher interviews at each preschool will be used in the analysis. Based on both these data sources, we currently develop definitions for each of the implementation components as well as a ranking system for each component, rated from 1 = ("not realized") to 3 ("completely realized"). Ratings will then be summarized to yield an overall degree of implementation. Intervention maintenance will be explored through interviews with preschool head teachers at 12 months, with data focusing around the extent to which the parents' projects have become an enduring part of the preschool's activity repertoire.

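### Research question 5 judges sustained effects by comparing month 6 with month 12, but the parent programme is still running at month 6, so the contrast mixes continued delivery with persistence

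*Protocol article*

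**What the plan says.** Under Research Questions, the fifth aim is that adding the parent programme "has sustained effects on primary and secondary outcomes stated above". A gloss in brackets defines this as the lack of a significant difference between the 6- and 12-month measurements. Month 6 is thus the reference and month 12 the follow-up.

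Evaluation Design fixes the visits: "Quantitative outcome measurements will be obtained before the start of the intervention (baseline assessment"), then "6 months after baseline assessment (at the end of the state-sponsored gym lesson programme) and at 12 months after baseline assessment". What ends at month 6 is the gym-lesson programme.

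Recruitment and randomization (text after the Figure 2 legend) gives the two arms. Control preschools "receive the state-sponsored programme's gym lessons over six months as the sole intervention". Intervention preschools receive the same lessons plus the parent programme, which "runs simultaneously with the gym lessons over the first six months, but continues for a total of at least nine months". The same section says that "the participatory intervention arm served as waiting list control during the first six months", which leaves the start of the programme relative to baseline less than clear.

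Maintenance is also looked at qualitatively: "Intervention maintenance will be explored through interviews with preschool head teachers at 12 months".

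**The concern.** A test of whether an effect lasts needs a reference at or near the time the tested component stops. Here the reference is tied to the end of the component that both arms share. The randomised component is then at most two thirds through its minimum length, and no child-level measurement is scheduled when it ends.

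This matters because sustainability is one of the trial's main arguments. The Background presents lasting behaviour change as the weakness of education-based programmes that a participatory approach might overcome. The Discussion speaks of effects continuing once the study's formal intervention is over, and of planning for that in the last parent meeting. A reader of a positive answer to question 5 would take it as persistence after support has stopped. Under the stated rule, further gain between months 6 and 9 could offset loss between months 9 and 12 and still be reported as sustained.

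The timing problem is separate from how the comparison is tested. Reading non-significance as proof of no change is a weakness of its own, but an equivalence margin would not move the reference visit.

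**Working it through.** The article gives no figure for the on-programme share of the interval, so there is nothing of its own to reproduce on this point. Its sample size does reproduce: 2 × ((1.960 + 1.282)/0.5)² = 84.06 per arm; design effect 1 + (21 − 1) × 0.1 = 3.0; 84.06 × 3.0 × 2 = 504.4 against the stated 504; and 504/0.9 = 560. The point below does not touch it.

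**Inputs**
- Visits at months 0, 6 and 12 (Evaluation Design).
- Gym lessons: 6 months in both arms (Recruitment and randomization).
- Parent programme length L: at least 9 months (same section).
- Start of the parent programme: assumed at about baseline.

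**Share of the 6-to-12-month interval spent on programme:** (L − 6)/(12 − 6). **Time off programme at the 12-month visit:** 12 − L.

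| Programme ends at month | On-programme, months 6–12 | Share | Off programme at month 12 |
|---|---|---|---|
| 9 (stated minimum) | 3 of 6 | 50% | 3 months |
| 10 (assumed) | 4 of 6 | 67% | 2 months |
| 11 (assumed) | 5 of 6 | 83% | 1 month |
| 12 (assumed) | 6 of 6 | 100% | 0 months |

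Only the first row rests on a stated length. The article's wording permits the others but does not establish them. At month 6, at most 6/9 = 67% of the programme has been delivered.

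**Sensitivity to the start.** If the programme starts s months after baseline (s from 0 to 3) and lasts the minimum 9 months, it ends at month 9 + s. The on-programme part of the interval is then 3 + s months and the time off programme at month 12 is 3 − s months. If the waiting-list sentence meant a 6-month delay from baseline (s = 6), the whole interval would be on programme: 12 − 6 = 6 of 6 months. A later start therefore makes the off-programme window smaller, never larger.

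**What changes between the two visits in the intervention arm.** At month 6 the gym lessons stop. From month 6 to at least month 9 the parent programme continues. After that it ends. A change from month 6 to month 12 within that arm combines all three. In a between-arm comparison the stop of the gym lessons is common to both arms, but the mixture of continued delivery and follow-up remains.

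**Illustration with assumed effects.** Suppose the between-arm effect is 0.3 SD at month 6, 0.5 SD at month 9 and 0.3 SD at month 12. The 6-to-12-month difference is 0.3 − 0.3 = 0, which the rule reads as sustained. Yet (0.5 − 0.3)/0.5 = 40% of the effect was lost within 3 months of the programme ending. With the article's SD of 38.1 counts per 15 seconds, that loss is 0.2 × 38.1 = 7.62 counts. This trajectory has no basis in the article and shows only what the rule could miss.

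**The case against.** The strongest reply is that question 5 defines its term operationally and never calls month 6 the end of the intervention. The article states openly what stops at month 6 and what continues. Month 6 is also when the combined package of lessons and parent programme ends, and whether the 6-month effect is still there at month 12 is a legitimate question. That stands as a description of the text. It does not remove the difficulty, because the article elsewhere uses sustainability to mean what happens after the formal intervention, and the 6-versus-12-month contrast does not isolate that.

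A second reply is that on and off programme is a blurred distinction here, since parents are meant to keep running their projects and maintenance is explored by interview at 12 months. This is fair, but the interviews are qualitative and do not supply a child-level outcome.

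Three stronger readings are tempting and should not be drawn:
- A reader might infer that the interval is mostly on-programme. At the stated nine months, with a start at baseline, the split is exactly 3 and 3. A majority needs a longer programme or a later start, and the article establishes neither.
- A reader might infer that the visits can show nothing about persistence. With a nine-month programme the 12-month visit lies about 3 months after it ends and does carry some short-term information.
- A reader might infer that questions 1 to 4 are mislabelled. They say only that effects are assessed at 6 months, which is correct.

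The timing counts also depend on a design figure that is not shown, and on the unclear waiting-list sentence. The bounds above cover that ambiguity, but the exact shares do not apply to any particular preschool.

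**Conclusion.** The point holds in a limited form. The reference visit for sustained effects marks the end of what both arms receive, while the randomised programme is still running. Assuming a start at about baseline, at least half of the 6-to-12-month interval is on-programme and the 12-month visit offers at most 3 months of follow-up after the programme. The contrast cannot separate continued delivery from persistence. What is affected is the sustainability conclusion alone; the primary comparison at 6 months, the model and the sample size stand. Whether any real loss of effect would be hidden cannot be known from the article.

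**What to change.** 1. Answer research question 5 with the between-arm difference at 12 months, described as the effect at most 3 months after the minimum programme ended. Stop using 6 versus 12 months as the test of sustained effect.
2. For each of the 17 intervention preschools, report the time from the end of the programme to the 12-month visit. End dates are not among the items that the article says the external teachers record, so derive them from the meeting and project documentation or ask at the 12-month head-teacher interview. This also makes the unclear start harmless, since the interval is counted from the actual end.
3. Claim no persistence beyond the observed interval. Where a preschool's programme was still running at month 12, its value is an on-programme value and should be described as such.

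Research questions 1 to 4 need no change.

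The cost is a rewording of one question and its conclusion, plus one date per intervention preschool. No visit or measurement of children is added. The real price is a weaker sustainability claim.
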